### Study outcomes

#### Primary outcome

The primary outcome of this trial is the changes in HbA1C.

#### Secondary outcomes

Secondary outcomes in this study include changes in other glycemic parameters such as fasting glucose, insulin, fructosamine, changes in lipid profile (triglyceride, total cholesterol, HDL-cholesterol, LDL-cholesterol), changes in inflammation (high-sensitivity C-reactive protein) and oxidative stress marker (plasma malondialdehyde), changes in anthropometry parameters (BMI, waist circumference), changes in metabolite profile (urine, serum), changes in safety parameters (liver profile and renal profile), changes in blood pressure, dietary pattern and physical activity.

### Procedure

After obtaining the informed consent, both groups will be required to attend clinical research center on 4 occasions- baseline, week 4, week 8 (end of study) and week 12 (post study follow-up). Subjects will be interviewed regarding their socio-demographic background at baseline. At each follow-up, all subjects will undergo a physical examination which include anthropometric, blood pressure, blood test, urine test and completed a dietary history questionnaire and international physical activity questionnaire (IPAQ).

Anthropometry measurements including weight, height and waist circumference will be measured. Body height will be measured using SECA stadiometer model 217 (SECA, Hamburg, Germany) to the nearest 0.1 cm. Body weight will be measured using a SECA electronic scale model 703 to the nearest 0.1 kg (SECA, Hamburg, Germany). Waist circumference in cm will be assessed midway between the lowest rib and the iliac crest using a non-stretchable tape measure. BMI will be calculated using World Health Organization classification [30]. Blood pressure will be measured using an automatic blood pressure monitor (Omron, Kyoto, Japan).

Blood sample will be drawn after an overnight fasting from the antecubital vein with patients in seated position. The volume of blood taken will be 10 ml, collected in four different pre-chilled tubes. A plain evacuated blood collecting tube will be used to collect 4 ml blood for metabolomic analysis. One milliliter will be taken in potassium oxalate/sodium fluoride tubes for fasting glucose. Another 1 ml blood sample will be taken in tubes containing ethylenediaminetetraacetic acid (EDTA) for HbA1C. The remainder 4 ml blood will be collected in the heparinized tube for other biochemistry parameters. Blood will be drawn by trained nurses and immediately placed on ice in the dim light environment. Blood sample that are collected will be centrifuged at 3000 rpm for 10 min at 4 °C to obtain the serum and plasma. 15 ml urine samples will be collected in the polyethylene containers. Blood and urine sample that are collected will be stored at −80 °C until further analysis.

### Biochemical assessments

All assays will be performed using Architect ci8200 analyzer (Abbott Laboratories, USA) except glycated hemoglobin (HbA1C) and malondialdehyde. Fasting blood glucose will be performed with a hexokinase-based method (Abbott Laboratories, USA). HbA1C will be measured with turbidimetric inhibition immunoassay method (Roche Diagnostics, Germany) using Cobas Integra 800 (Roche Diagnostics, Germany). Serum total cholesterol, triglycerides, high-density lipoprotein (HDL) cholesterol, and low-density lipoprotein (LDL) cholesterol levels will be quantified by commercially available enzymatic assay kits (Abbott Diagnostics, USA). High sensitivity C-reactive protein will be determined using the quantitative immunoturbidimetric method. For renal function test, sodium, potassium and chloride will be determined by potentiometric using solid state ion-selective electrode, urea will be determined by enzymatic method and creatinine will be determined using the kinetic method. For liver function test, total protein will be determined using biuret endpoint, albumin will be determined by direct colorimetric determination, total bilirubin will be determined by diazonium salt method whereas alkaline phosphatase, aspartate aminotransferase, and alanine aminotransferase will be determined by the kinetic method. Malondialdehyde will be measured by thiobarbituric acid reactive substances assay using UV spectrophotometer (UV-1601, Shimadzu, Japan) [31]. All biochemical assays will be performed by B. P. Clinical Lab.

### Dietary intake assessment

Dietary intake will be assessed with a dietary history questionnaire. Patients will be requested to provide complete food descriptions including food and drinks (brand names), food preparation (ingredients) and cooking method (such as deep-frying, stir-frying, boiling, grilling, barbecue, roasting, and steaming) as detail as possible in a week. Pictures of food commonly consumed in Malaysia, together with a set of common household measurement tools (glass, cup, Chinese rice bowls, soup bowls, plates, teaspoon and tablespoon) will be provided to assist subjects in estimating the portion sizes of the food.

The nutrient analysis will be carried out using Nutritionist Pro^™^ diet analysis software (version 2.5, Axxya Systems, USA). This software contains several databases including Nutrient composition of Malaysian foods and the United States Department of Agriculture (USDA). For food items unavailable in Nutritionist Pro diet analysis software, database will be obtained from Singapore Food Composition Guide (Health Promotion Board, 2003) and all the nutrients for food items will be manually added to Nutritionist Pro diet analysis software.

### Physical activity levels assessment

International Physical Activity Questionnaire (IPAQ) will be administered to assess the physical activity level of the subjects. The items in the IPAQ form consist of scores on walking, moderate-intensity and vigorous-intensity activity. The IPAQ’s total score for physical activity level will be expressed as metabolic equivalents per minute (MET-min) per week, sums the duration (in minutes) and frequency of walking, moderate-intensity and vigorous-intensity activities. Levels of physical activity will be category into low, moderate and high as per IPAQ criteria [32].

### Statistical analysis

All clinical data will be performed using SPSS version 21 for windows (SPSS Inc, Chicago, USA). Data will be expressed as mean ± SD for continuous parameters, and percentage for categorical parameters. Normality tests assessed through Shapiro-Wilk tests will be carried out on each parameter before analysis. For baseline characteristic, independent t-test will be used to compare the difference in the study outcomes between the diabetic treatment and control group. All outcome measurements will be evaluated based on intention-to-treat analysis using all randomized patients who have attended the blood test at baseline. Missing data will be imputed using “last observation carried forward” method. The comparison within each group will be carried out using paired t-test, while the changes between the two groups will be conducted using independent t-test. A *p*-value of less than 0.05 will be considered as significant. Data will be reported with adherence to the CONSORT 2010 guidelines [33].

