The objective of this trial is to investigate the effectiveness and safety of *C. caudatus* in patients with type 2 diabetes by addressing the following hypothesis (1) *C. caudatus* supplementation will improve the glycemic status in patients with type 2 diabetes (2) *C. caudatus* supplementation will improve inflammation marker, oxidative stress marker and lipid profile in patients with type 2 diabetes (3) *C. caudatus* supplementation is safe and will not result in adverse effects (4) the therapeutic effect of *C. caudatus* will result in changes in urine and serum metabolome.

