#### Diabetic control (C) group

The diabetic control (C) group will be asked to abstain from consuming *C. caudatus* for 8 weeks . Both groups will be given standard lifestyle interventions which include medical nutrition therapy and physical activity enforcement). In addition, both groups will be educated for the concepts of carbohydrate exchange and serving sizes. Patients in diabetic control (C) group will be encouraged to eat the same serving of fruits and vegetable as the *C. caudatus* treated (U) group. Likewise, patients in diabetic control (C) group will be advised to perform self-monitoring blood glucose. Glucometer and strips will be given to both groups to record three values daily (after fasting, before a meal and two hours after a meal). All the patients will be educated on how to use the glucometer.

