### Adherence

To check patients’ compliance during the 8 weeks, the researcher will interview them weekly by telephone. In *C. caudatus* treated (U) group, patients will be interviewed to discern whether they were consuming *C. caudatus* and to address all their concerns. In diabetic control (C) group, phone calls are made weekly to emphasize the importance of lifestyle modification.

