### Patient safety

Patients will be monitored weekly during the study period and all the occurrence of the adverse events will be assessed by patient interviews. All anticipated adverse events such as loose stools, abdominal discomfort, bloating, flatulence, sign of hypoglycemia, sign of hyperglycemia will be recorded. Additionally, liver profile and renal profile will be measured at every visit.

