## Discussion

Type 2 diabetes is a common chronic disease worldwide. Medicinal plants are gaining tremendous resurgence of interest among researchers recently because of their health benefits [14, 34]. *C. caudatus* is widely consumed among the local Malays in South East Asia and its potential medicinal benefits have been reported [16]. The strength of this trial is that, it is the first randomized controlled trial to determine the effectiveness of *C. caudatus* on the outcomes measurement such as glycemic status, lipid profile, oxidative stress marker, and inflammation marker which are important parameters in patients with type 2 diabetes.

To the best of knowledge, there is no established data on herb-drug interaction of *C. caudatus*. Therefore, an interim analysis will be carried out to monitor the safety of consuming *C. caudatus* throughout the study. The results of this trial will provide clinical evidence on the effectiveness and safety of *C. caudatus* supplementation in patients with type 2 diabetes. Moreover, metabolomics is a powerful tool to study the altered metabolism, identify short-term changes in biological fluids and serve as biomarker detection [26]. Metabolomics approach used in this study will fill in the gap and provide a better understanding of metabolite profile following the supplementation of *C. caudatus*. Therefore, results from this study will contribute to the knowledge on the therapeutic effect mechanism of *C. caudatus*.

To date, the most commonly used metabolomics technologies for metabolomics study are nuclear magnetic resonance (NMR) spectroscopy, and mass spectrometry (MS) such as liquid chromatography-MS (LC-MS) and gas chromatography-MS (GC-MS) [26]. GC-MS and LC-MS are robust technologies that offer high sensitivity in metabolites detection [26]. However, both of the techniques have some drawbacks including relatively slower acquisition time, requires sample derivatization (GC-MS), consumption of sample (both LC-MS and GC-MS), chromatography can drift during a sample run, which makes data processing difficult (LC-MS), and peak assignment is a major challenge (LCMS) [35, 36]. On the other hand, NMR offers some advantages such as its ability to provide high-resolution spectra, requires relatively simpler sample preparation hence more rapid analysis and more importantly non-destructive of the sample. However, NMR-based metabolomics has a lower sensitivity compared to MS [35–37].

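### Intention-to-treat is the only between-group analysis set fixed for the safety outcomes; a supportive analysis by actual leaf consumption should stand beside it, because non-adherence pulls the result toward no harm

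*Protocol article*

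**What the plan says.** The Statistical analysis section sets one rule for the analysis set: "All outcome measurements will be evaluated based on intention-to-treat analysis using all randomized patients who have attended the blood test at baseline". It makes no exception for safety. Missing values are carried forward from the last observation, and changes are compared between arms by an independent t-test at p < 0.05.

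The Secondary outcomes section includes "changes in safety parameters (liver profile and renal profile" among the outcomes, so the rule applies to them directly. Adverse events appear only under Patient safety, where "all the occurrence of the adverse events will be assessed by patient interviews". They are not in the outcome list.

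The third hypothesis at the end of the Background is that the plant's "supplementation is safe and will not result in adverse effects".

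On exposure, treated patients are to eat 15 g of raw leaf daily for 8 weeks. In the Adherence section these "patients will be interviewed to discern whether they were consuming" the leaf. For the other arm, "The diabetic control (C) group will be asked to abstain from consuming" the plant, but the weekly contact is described differently: "phone calls are made weekly to emphasize the importance of lifestyle modification". The Discussion says that the plant "is widely consumed among the local Malays in South East Asia". Both arms complete a dietary history questionnaire at each follow-up (Procedure).

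**The concern.** Analysing patients as randomised moves the two arms toward each other whenever patients do not follow their allocation. For hypotheses that predict a benefit, this makes a positive claim harder to reach, which is the cautious direction. For a hypothesis that predicts no harm, it works the other way: a difference that is diluted and then not significant can be read as support. No margin for acceptable harm is stated, so p < 0.05 is the only between-group criterion.

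Both kinds of departure are plausible from the article's own facts. A raw leaf must be eaten every day for 8 weeks. Controls are asked to avoid a common local food, and no check on that is described. The Discussion also says that herb-drug interaction data are not established, so a harm signal missed for this reason would matter.

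**Working it through.** **Figures in the plan.** None exists for safety. The only design figure is 50 per arm, set for HbA1c (difference 1 %, SD 1.75 %, 80 % power). The standardised difference is 1/1.75 = 0.57, and a two-sided calculation needs 49 per arm before any allowance for drop-out. Only the arm size of 50 is used below. Whether 50 also covers the 30 % drop-out is a separate matter.

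**Step 1, reach of the rule.** All outcomes are under intention-to-treat, and the liver and renal profiles are outcomes. Adverse events are not named as outcomes, so the calculation below uses a continuous liver or renal parameter.

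**Step 2, dilution.** Let Δ be the true mean change caused by eating the leaf, u the share of treated patients who do not eat it, and c the share of controls who do.

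- Expected excess in the treated arm: (1 − u)Δ
- Expected excess in the control arm: cΔ
- Expected observed difference: (1 − u − c)Δ

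This takes harm to come only from eating the leaf, and it gives a control who eats any leaf the full effect, which is an upper-end treatment of occasional intake.

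**Step 3, power.** At 50 per arm the standard error of the difference is √(2/50) = 0.20 SD. The harm detectable with 80 % power (two-sided 5 %) is (1.960 + 0.842) × 0.20 = 0.56 SD by the normal approximation, or 0.57 SD by the t-test. Power after dilution is Φ[2.802 × (1 − u − c) − 1.960]:

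| u (assumed) | c (assumed) | Harm retained | Power |
|---|---|---|---|
| 0 | 0 | 100 % | 80 % |
| 10 % | 0 | 90 % | 71 % |
| 10 % | 10 % | 80 % | 61 % |
| 20 % | 10 % | 70 % | 50 % |
| 30 % | 10 % | 60 % | 39 % |
| 30 % | 20 % | 50 % | 29 % |

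For example, at u = c = 10 %: 2.802 × 0.8 − 1.960 = 0.281, and Φ(0.281) = 0.61. The t-test gives the same percentages.

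**Step 4, what a comparison by consumption would recover.** If every non-eater never ate any leaf and all intake were reported correctly, the full 0.57 SD would be compared in smaller groups:

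- u = c = 10 %: 45 v 45, power 76 % (against 61 % as randomised).
- u = 30 %, c = 10 %: 35 v 45, power 70 % (against 39 % as randomised).

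If that 30 % ate one portion and then stopped, a rule of at least one portion keeps them as exposed. The comparison is then 50 v 45 with 70 % of the harm retained, and power is about 48 %. Most of the gain is lost, so the exposure measure has to be graded.

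**Step 5, adverse events, by extension only.** Assume an event risk of 25 % in eaters and 5 % in non-eaters, with a two-sided Fisher test at 50 v 50. Power is 75 % with full adherence (20 points), 51 % at u = c = 10 % (16 points) and 31 % at u = 30 %, c = 10 % (12 points). Comparing eaters with abstainers gives 71 % (45 v 45) and 70 % (35 v 45). If the 30 % ate once and stopped, 19 % v 5 % in 50 v 45 gives 14 points and 50 %.

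**The case against.** The strongest reply is that an as-randomised safety comparison is sound. It is the only one protected by randomisation, and replacing it would exchange a known dilution for confounding by the reasons people stop. That stands. A reader might infer that intention-to-treat is simply the wrong set for safety and should be confined to effectiveness. The documents do not support that.

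Nor is the randomised contrast the only safety information. The plan has weekly adverse-event interviews, within-group paired tests and an interim safety analysis (Discussion). The paired test in the treated arm is not affected by controls eating the leaf. It is still diluted by treated patients who do not, and it has no comparator.

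The size is also open to challenge. Neither u nor c is in the article. A reader might take the planned 30 % drop-out as the share of non-eaters, but a patient may eat the leaf and leave because of symptoms. The remark on local consumption describes a population, not the trial's controls. A reader might also apply the rule to adverse events as firmly as to the laboratory profiles. The text does not go that far, and a condensed article may leave their analysis to a fuller document.

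Finally, an exposure analysis can have its own bias toward safety. If values taken after stopping are cut, harm that caused the stopping disappears. Intake is self-reported in an open-label trial. These points shape the remedy; they do not remove the need for it.

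**Conclusion.** The point holds in a limited form. For the liver and renal profiles, the plan fixes intention-to-treat as its only between-group analysis set, under a hypothesis that predicts no harm. If the leaf causes harm, any non-eating in the treated arm or eating among controls moves that comparison toward the predicted answer. This follows from a stated rule and is not a missing detail.

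The direction needs only that harm comes from eating the leaf and that u or c is above zero. The size is illustrative: a harm detectable with 80 % power is seen with about 61 % power at u = c = 10 % and about 39 % at u = 30 %, c = 10 %. The documents do not show that dilution of this extent will occur. The primary outcome is not affected. This is a cheap improvement to the safety analysis and gives no reason to drop the randomised comparison.

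**What to change.** Keep the as-randomised safety comparison. Add to the Statistical analysis section a pre-specified supportive safety analysis by actual consumption, covering the liver and renal profiles and adverse events:

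- Classify patients in both arms by reported intake, using the weekly calls for the treated arm and the dietary history questionnaire for both arms.
- Grade exposure by amount or duration eaten, and do not rely only on whether at least one portion was eaten.
- Use observed values without carrying the last one forward. Under carry-forward, a patient who leaves before week 4 contributes a change of zero.
- Keep values measured after a patient stops eating the leaf, so that harm leading to stopping is not removed.

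The cost is a short addition to the text and one extra table, from intake data already planned. The downside is that the table rests on self-report and is not protected by randomisation, so it is read beside the as-randomised result and does not replace it.

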### Sample size

A total of 50 patients are required in each group to detect a significant mean difference of 1 % HbA1C [29], 1.75 % standard deviation [29], 95 % confidence level and 80 % power, with additional drop-out rate of 30 %.

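### Carrying the last value forward as the sole missing-data rule, with 30 % drop-out planned, biases the estimated week-8 HbA1c difference

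*Protocol article*

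**What the plan says.** The Statistical analysis section names one way of handling missing data, "last observation carried forward". It applies to every outcome, in all randomised patients who gave a baseline blood sample. Changes are then compared between arms by an independent t-test. A baseline value alone is therefore enough to enter the analysis, and it is the value that gets carried.

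The Sample size section allows for an "additional drop-out rate of 30" %. The Procedure section sets visits at baseline, week 4, "week 8 (end of study) and week 12 (post study follow-up"). Supplementation lasts 8 weeks (Intervention). The outcome statement reads "The primary outcome of this trial is the changes in HbA1C" and names no visit. Week 8 as the primary time point is inferred here from the treatment length and the end-of-study label.

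**The concern.** Carrying a value forward assumes that HbA1c stops moving when a patient leaves. The design expects the opposite: both arms receive nutrition therapy and physical activity advice, and the trial's first hypothesis is that the supplement improves glycaemia. Given the visit schedule, the rule acts in three ways:

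- A patient lost before week 4 contributes a week-8 change of exactly zero.
- A patient lost between weeks 4 and 8 contributes a value taken halfway through the course.
- A patient missing only week 12 contributes an end-of-treatment value to the post-treatment visit, which can make an effect look sustained after supplementation has stopped.

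At stake is the size of the primary estimate and, if the arms lose patients at different rates, also its direction. Unequal loss is possible because patients are not blinded and only one arm has to eat the leaves every day.

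**Working it through.** **Inputs from the article.** Difference 1 % and 50 per arm ("A total of 50 patients are required in each group to detect a significant mean difference of 1 % HbA1C"); "1.75 % standard deviation"; "95 % confidence level and 80 % power"; drop-out 30 %; visits as above.

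**Inputs assumed, because the article does not give them.** s, the share of drop-outs who leave before week 4 (0 to 1); f, the share of the week-8 change present at week 4 (0.5, with 0.25 to 0.75 as a range); m, the improvement common to both arms; the drop-out split between arms; drop-out unrelated to outcome. SD 1.75 is used as the SD of change.

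**The plan's own figure.** n per arm = 2(z₁ + z₂)²σ²/δ².

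- Two-sided 5 %: 2 × (1.960 + 0.842)² × 1.75² / 1² = 48.1, so 49. With the drop-out allowance, 49/0.70 = 70.
- One-sided 5 %: 2 × (1.645 + 0.842)² × 1.75² = 37.9, so 38, and 38 × 1.30 = 49.4, so 50.

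The stated 50 is thus the two-sided figure with almost no allowance, or a one-sided figure times 1.30. That is a separate matter. What counts here is that 30 % of 50 is 15, which leaves 35 observed per arm.

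**Equal drop-out d in both arms.** Expected week-8 difference after carrying forward = Δ × [(1 − d) + d(1 − s)f]. With Δ = −1.0, d = 0.30, f = 0.5:

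- all lost before week 4 (s = 1): −1.0 × 0.70 = −0.70
- half before, half after (s = 0.5): −(0.70 + 0.30 × 0.5 × 0.5) = −0.775
- all lost after week 4 (s = 0): −(0.70 + 0.30 × 0.5) = −0.85

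With f from 0.25 to 0.75, the second becomes −0.74 to −0.81 and the third −0.775 to −0.925. With less drop-out, over the same ranges of s and f, the estimate is −0.90 to −0.975 at 10 % and −0.80 to −0.95 at 20 %. Simulation (50 per arm, 4,000 to 5,000 runs) gave −0.70 to −0.71, −0.77 to −0.78 and −0.84 to −0.86 for the three cases. Analysis of the observed week-8 values gave −1.00.

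**Power and test size under equal drop-out.** With half lost before week 4, the simulated estimate over its standard error is 0.778/0.319 = 2.44 after carrying forward and 1.005/0.418 = 2.40 in observed data. The estimate and its standard error shrink together. Simulated power was 0.63 to 0.71 against 0.64 to 0.67. With no true effect, the rejection rate was 0.046 to 0.055.

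**Unequal drop-out, no true effect.** The carried-forward mean improvement in an arm is m × [1 − d(s + (1 − s)(1 − f))]. The spurious difference is therefore m × (difference in drop-out) × [s + (1 − s)(1 − f)], in favour of the arm that loses fewer patients. With m = 1.0, 20 % against 40 %, f = 0.5:

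| Timing of loss | Spurious difference | Simulated type I error |
|---|---|---|
| all before week 4 | 1.0 × 0.20 × 1 = 0.20 | 0.09 to 0.10 |
| half before, half after | 1.0 × 0.20 × 0.75 = 0.15 | 0.074 to 0.076 |
| all after week 4 | 1.0 × 0.20 × 0.5 = 0.10 | 0.056 |

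With m = 0.5 and half lost early, the spurious difference is 0.5 × 0.20 × 0.75 = 0.075 and the error 0.053 to 0.056. With m = 0.5 and 25 % against 35 %, the error is 0.050 to 0.057 whatever the timing.

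**Unequal drop-out, true difference −1.0** (m = 0.5, s = f = 0.5):

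- 40 % lost on treatment, 20 % on control: −[1.5 × (1 − 0.40 × 0.75) − 0.5 × (1 − 0.20 × 0.75)] = −(1.05 − 0.425) = −0.625
- reversed: −[1.5 × 0.85 − 0.5 × 0.70] = −(1.275 − 0.35) = −0.925

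**The case against.** The rule can be defended as conservative, and with equal drop-out that is fair: the estimate moves toward no effect and false positives do not increase. The defence fails once the arms lose patients at different rates while both are improving.

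Four stronger readings are tempting, and the documents do not support them.

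- **That the rule costs power.** Holding the SD at 1.75 while shrinking the difference suggests power as low as 0.52. But carried-forward zeros also reduce the SD, and power is about the same as in an observed-data analysis, roughly 0.65 in each.
- **That the t-test's standard error is wrong because filled-in values count as data.** In simulation it matched the sampling SD of the carried-forward estimate (0.319 and 0.319; 0.305 and 0.302). What is overstated is the information about the true week-8 difference: 50 patients per arm appear to inform it when about 35 do.
- **That the type I error is 10 %.** This is a worst case. It needs one arm to lose twice as many patients, all before week 4, and a full 1.0 % improvement in both arms. Nothing in the article supports a 20 % against 40 % split.
- **That controls get nothing and so will leave.** They get the same lifestyle intervention, a glucometer with strips, and weekly calls. Unequal loss is possible but not shown.

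It is also true that 30 % is a planning allowance with no visit attached. Patients lost after week 8 have an observed week-8 value, so 30 % missing at week 8 is an upper bound. An analysis plan not shown may add sensitivity analyses, but these would not change the rule stated for the primary comparison.

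**Conclusion.** The point stands as one about bias in the estimate. If the full 30 % per arm are missing at week 8, a true −1.0 % difference is reported as about −0.70 to −0.85, an understatement of 15 to 30 %, assuming half the effect is present by week 4. Fewer losses give proportionately less bias. Observed-data analysis is unbiased in these scenarios because drop-out was assumed ignorable; that is not guaranteed in the trial.

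With equal drop-out, test size and power are not the problem. With unequal drop-out the bias can go either way: 0.10 to 0.20 % and a type I error of about 0.06 to 0.10 in the assumed null case, less in milder ones. The drop-out splits, timings and common improvements are assumptions, and week 8 as the primary visit is an inference.

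**What to change.** Replace carrying forward plus the t-test as the primary analysis with a likelihood-based mixed model for repeated measures on all observed HbA1c values.

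- Include baseline as one of the outcomes, with the arm means constrained equal at baseline; fit visit, arm-by-visit and an unstructured covariance. Patients with only a baseline value then stay in the analysis set that the article defines. A model with baseline as a covariate and only post-baseline outcomes would drop them.
- Name the week-8 (end of treatment) arm contrast as primary.
- Keep carrying forward at most as a sensitivity analysis.
- Add one delta-adjusted (tipping-point) multiple-imputation analysis for non-ignorable drop-out.

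The cost is new wording in the statistical section and a little more analysis work. The visits and measurements are already scheduled, and no extra patients are needed for this change. The downside is that the model relies on data being missing at random, which the tipping-point analysis is there to probe.

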**Methods and design:**

This is a single-center, randomized, controlled, two-arm parallel design clinical trial that will be carried out in a tertiary hospital in Malaysia. In this study, 100 patients diagnosed with type 2 diabetes will be enrolled. Diabetic patients who meet the eligibility criteria will be randomly allocated to two groups, which are diabetic *C. caudatus* treated(U) group and diabetic control (C) group. Primary and secondary outcomes will be measured at baseline, 4, 8, and 12 weeks. The serum and urine metabolome of both groups will be examined using proton NMR spectroscopy.

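### The between-arm t-test of change leaves baseline HbA1c unused as a covariate, and paired tests within arms stand beside it with no statement of which test decides efficacy

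*Protocol article*

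**What the plan says.** The Primary outcome section states: "The primary outcome of this trial is the changes in HbA1C". The Statistical analysis section fixes two kinds of test for the outcomes. Within arms: "The comparison within each group will be carried out using paired t-test". Between arms: "the changes between the two groups will be conducted using independent t-test". A single threshold covers both, a p-"value of less than 0.05 will be considered as significant". No baseline covariate is named, and no sentence says which of the two tests decides efficacy.

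The baseline value is in hand. The abstract says: "Primary and secondary outcomes will be measured at baseline, 4, 8, and 12 weeks". The analysis set is defined by it, "using all randomized patients who have attended the blood test at baseline".

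On co-intervention, the section on the control group says: "Both groups will be given standard lifestyle interventions". Glucose self-monitoring is also advised in both arms.

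**The concern.** There are two separate issues.

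**Precision.** Subtracting baseline fixes its coefficient at 1. When the correlation between baseline and follow-up is below 1, that over-corrects. With equal SDs, a chance baseline difference D between arms shifts the expected difference in change by -(1-rho)D, through regression to the mean. ANCOVA estimates the coefficient from the data, removes this shift and usually narrows the confidence interval. The covariate is already collected for everyone analysed.

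**Within-arm tests.** A paired test compares an arm with its own past. Entry requires a last HbA1c above 7 %, and both arms get nutrition therapy and physical activity advice, so both may fall whatever the plant does. Hypotheses (1) and (2) in the Background say that supplementation will improve outcomes, without reference to control. With no deciding test named, a significant fall in the treated arm beside a non-significant one in the control arm could be reported as an effect of the plant.

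**Working it through.** **Inputs from the Sample size section:** difference 1 % HbA1c; SD 1.75 % (not said whether of change or of a single value); "95 % confidence level and 80 % power"; 30 % drop-out; 50 per arm. Two-sided testing is assumed.

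**The plan's own figure.** n per arm = 2 × [1.75 × (1.960 + 0.842) / 1]² = 48.1, so 49 (50 with the exact t-test). The stated 50 therefore matches the inputs before drop-out. A 30 % loss leaves 50 × 0.70 = 35 completers per arm.

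**Variance ratio.** With equal SDs at both times and correlation rho, which the document does not give:

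Var(ANCOVA) / Var(change) = (1 - rho²) / [2(1 - rho)] = (1 + rho) / 2.

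**Power to detect 1 %, taking 1.75 as the SD of change.** The ANCOVA residual SD on this scale is 1.75 × √[(1 + rho)/2]. Completer power is by noncentral t, with one degree of freedom spent on the covariate. The last column is a simulation of the planned set of 50 per arm, with 30 % (15 per arm) carried forward from baseline. That is a worst case in which every drop-out leaves before week 4, and it shrinks the expected difference to 0.70 × 1 = 0.70.

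| rho | Variance ratio | ANCOVA, 35 completers per arm | ANCOVA, 50 per arm with carry-forward |
|---|---|---|---|
| 0.4 | 0.70 | 80 % | about 74 % |
| 0.5 | 0.75 | 78 % | about 72 % |
| 0.7 | 0.85 | 72 % | about 69 % |
| 0.8 | 0.90 | 70 % | about 67 % |

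The unadjusted t-test of change has 65 % power with 35 completers and about 64 % with carry-forward. In numbers of patients, the change score needs 1/0.90 to 1/0.70 times as many, that is 11 % to 43 % more.

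**If 1.75 is the SD of a single value.** The SD of change is then 1.75 × √[2(1 - rho)]. With 35 completers per arm, power goes from 58 % to 73 % at rho 0.4, 65 % to 78 % at 0.5, 86 % to 91 % at 0.7, and 96 % to 98 % at 0.8.

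**If the baseline spread is narrower.** With baseline SD equal to k times follow-up SD, the ratio is (1 - rho²) / (1 + k² - 2k·rho). At an assumed k = 0.8:
- rho 0.5: 0.75/0.84 = 0.89
- rho 0.7: 0.51/0.52 = 0.98
- rho 0.8: 0.36/0.36 = 1.00

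**Within-arm tests.** Suppose both arms truly improve by the same amount m and the plant does nothing (SD of change 1.75, 50 per arm). Each paired test is significant with probability p, from a noncentral t with noncentrality m√50/1.75. The arms are independent, so the treated arm is significant and the control arm is not with probability p(1 - p), which cannot exceed 0.25.

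| m | p | p(1 - p) |
|---|---|---|
| 0.1 | 0.068 | 6 % |
| 0.2 | 0.124 | 11 % |
| 0.35 | 0.284 | 20 % |
| 0.5 | 0.508 | 25 % |
| 0.7 | 0.792 | 16 % |
| 1.0 | 0.977 | 2 % |

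A between-arm test at two-sided 0.05 would falsely favour treatment in 2.5 % of such trials.

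**The case against.** The strongest reply is that nothing here is an error. Under randomisation the t-test of change is valid and unbiased, and it matches an outcome defined as a change. That stands: a reader might infer that the primary test is invalid, and the document does not support that.

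A reader might also infer that the paired tests form part of the primary comparison, or that efficacy will be claimed from them. The text lists them beside the between-arm test, does not call them primary and draws no conclusion from them. What remains is that it does not say which test decides. Nor would ANCOVA by itself prevent within-arm claims; that needs a separate sentence.

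The size of the gain is also open to challenge, and rightly. It depends on an unstated correlation, on what the 1.75 describes, on equal SDs and on how drop-outs are handled. Entry above 7 % may narrow the baseline spread, and the gain then nearly vanishes at high rho. The 25 % figure is a mathematical ceiling, not an expected rate.

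Finally, the article mentions no stratification by HbA1c, but a condensed article may leave that to the full protocol, so nothing here relies on its absence. The baseline t-tests are not used to choose an adjustment, and dropping them is a matter of reporting practice.

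**Conclusion.** The point holds as a question of efficiency and clarity. The planned comparison is valid but gives up precision that the collected data would supply. The variance ratio is 0.70 to 0.90 for an assumed rho of 0.4 to 0.8 with equal SDs, and nearer 1 with a narrower baseline spread. That ANCOVA is at least as precise is a large-sample result.

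If 1.75 is the SD of change, power rises from 65 % to 70-80 % among 35 completers per arm, and from about 64 % to 67-74 % in the worst-case carry-forward set. A reader might infer that adjustment restores the planned 80 %. It does so only for completers at the low end of the correlation range, and it does not repair last-observation-carried-forward imputation.

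The within-arm tests are a separate weakness. With equal improvement of 0.1 to 1.0 in both arms and no plant effect, the misleading pattern arises in 2 % to at most 25 % of trials (SD of change 1.75, 50 per arm). The document gives no expected common improvement, so the range is what can be said.

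**What to change.** In the Statistical analysis section:

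1. Analyse week-8 HbA1c by ANCOVA with treatment arm and baseline HbA1c as terms. Treat each continuous secondary outcome the same way, with its own baseline as covariate.
2. State that the adjusted between-arm difference, with its 95 % confidence interval, is the only basis for an efficacy conclusion.
3. Report within-arm changes as mean and SD without p-values, labelled descriptive.
4. Optionally, drop the baseline t-tests and present baseline characteristics descriptively.

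The cost is wording only. No new data, visits or patients are needed.
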